#### Implementation

JS will be responsible for the overall management of the trial, including the generation of the allocation sequence, and assignation of delegations to either the intervention or control group. While in Tunisia, JS will be working under the auspices of members of the Ministry of Health and the WHO office. They will help ensure the successful implementation of the training program in Tunis and Sousse.

#### Blinding

To protect against result contamination, delegations and not individuals will be randomized. Given the geographic distance between each delegation included in this trial, it is very unlikely that GPs from different delegations will share information during and after the training sessions. Selection bias will be avoided by randomization.

Members of the Ministry of Health and WHO office in Tunisia working to ensure the successful implementation of this training program in Tunis and Sousse will be blinded to the allocation of delegations.

### Data collection, management, and analysis

#### Data collection and methods

Questionnaires will be administered to the intervention and control groups at different times. These include questionnaires on socio-demographics, knowledge, attitudes, self-efficacy and mental health practice. The socio-demographic questionnaire will include information on GPs’ sex, age, number of years working in primary care, percentage of time dedicated to mental health in primary care, education, previous mental health training, and work location.

The knowledge questionnaire has been developed by the WHO to accompany the mhGAP-IG and training package. However, it has been adapted to conform to the modules that have been chosen for the purposes of this trial.

The *Mental Illness Clinicians’ Attitudes (MICA) Scale (version 4)* [54, 55] was chosen to assess GPs’ attitudes in this trial. This scale is a modified version of the *Mental Illness Clinicians’ Attitudes (MICA) Scale (version 2)*, which aims to assess attitudes of medical students towards mental illness and the mental health field. Kassam et al. (2010) [54], by modifying this scale, developed a version that can be used with students and health care professionals of any health discipline. It is of interest for this trial because most of the other scales that aim to assess health professionals’ attitudes towards mental illness have questionable psychometric properties [55]. The *MICA Scale (version 4)* has 16-items, and answers range from ‘strongly agree’ to ‘strongly disagree’. It was shown to have adequate internal consistency and test-retest properties [55].

A self-efficacy questionnaire was developed for the purposes of this trial. Self-efficacy is a concept first introduced by Bandura [56], and is part of his social cognitive theory as a “key psychological construct with regards to how people adapt to their environments where new skills are developed” [57]. More specifically, self-efficacy refers to people’s beliefs in their capabilities, which influence performance attainment, achievement of outcomes, and behavioural change [56–58]. For these reasons, assessment of perceived clinical self-efficacy is of interest when evaluating training programs because positive effects on self-efficacy scales should translate into practice change [59]. Bandura (2006) [58] suggests that the best way to measure self-efficacy in a study is to develop specific scales per tasks to be explored. In this case, the explored task is the perceived clinical self-efficacy in mental health detection, treatment, and management at the level of primary care, particularly for the selected training modules. The developed self-efficacy questionnaire is thus comprised of questions aiming to understand GPs’ judgement of capabilities in detecting and diagnosing depression; psychosis; suicide/self-harm; alcohol use disorders; and drug use disorders; as well as treating and managing patients who present symptoms related to these disorders. An overall assessment that reflects self-efficacy will then be generated by averaging all the constructed domains of the scale.

A mental health practice questionnaire based on the *Mental Neurological and Substance Use Patient Visit Summary* developed by the WHO for the mhGAP Support and Supervision Guide will be administered. The purpose of administering this questionnaire is to collect the number of total cases (i.e., new, follow-up, or referred cases) before and after the training intervention, as well as patient socio-demographics.

Data will be collected at 4 times. At baseline (T-1, or before the training offered to the intervention group), GPs in both groups will be administered the 5 questionnaires (i.e., socio-demographic, knowledge, attitudes, self-efficacy and mental health practice). Post-intervention group training (T-2), both the intervention and control groups will be administered the same questionnaires, minus the socio-demographic questionnaire. The reason for the administration of the same questionnaires to the control group at T-2 is to account for contamination between groups during the intervention group training, and will serve as the pre-training measure for this group, also a way to maximize our sample. T-2 therefore is also known as the pre-test control group training measure. Post-test control group training (T-3), the control group will be administered the same knowledge, attitude, self-efficacy and mental health practice questionnaires. One year after the completion of the intervention group training (T-4), the groups will be administered the knowledge, attitude, self-efficacy and mental health practice questionnaires to assess whether the results of the training program were maintained over time.

#### Data management

JS, who is under the supervision of FC, NL, and MP, will be responsible for data collection, entry, coding, and management.

#### Statistical methods

All participants will be included in the analysis. This type of analysis is called intention-to-treat and is considered the best way to preserve the effects of randomization [53, 60]. Answers generated by questionnaires and surveys will be analyzed using SPSS Statistical Software (version 24).

T-tests on the difference in cluster means between the intervention and control groups [53] will be assessed for the questionnaires administered to the GPs. Two-tailed P values of less than 0.05 will be considered statistically significant. While the aforementioned t-tests take into account cluster level analysis, individual level analysis is discarded, which can underestimate the power of the analysis and generate misleading conclusions about the intervention [53, 61]. Adjustments can be made to the t-tests in order to account for individual level analysis. Campbell et al. (2000) [61] suggest that the t-test values (i.e., the differences between groups) should be divided by the square root of the design effect (i.e., 1 + (m-1) ICC). Two-tailed P values of less than 0.05 will be considered statistically significant. Individual level analysis will result in a higher significance level, compared with cluster level analysis [61].

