#### Sample size

This trial will answer a number of important questions regarding study design, namely: What is the estimated effect size and ICC of a mental health training based on the mhGAP-IG? These parameters, to our knowledge, were not available at the time this protocol was written and defended (June 2015), and will thus make significant contribution to knowledge on the mhGAP-IG.

Following consultation with members of the Ministry of Health in Tunisia, the recommended average number of GPs to be recruited in the cluster (i.e., the delegation, many of which comprise the governorate) was suggested to be 15. While some studies using a cluster RCT to evaluate the effectiveness of a mental health training program offered to GPs in HICs do not report attrition [49–51], we are concerned that the evidence does not reflect the sampling realities in LMICs. For this reason, we aim to recruit 19 GPs per delegation, to be sure we account for a maximum of 20% attrition rate per cluster [52, 53]. Table 1 highlights the estimated sample size and number of clusters for the trial.

**Table 1 Tab1:** The sample size and number of clusters in the trial

PARAMETERS	#
n (total number of GPs)	722
# clusters (delegation)	38
n cluster (GPs on average per cluster)	19

Using the statistical software G*Power 3.1, the effect size can be calculated after data collection. Parameters will be set at: 1) test family: *t* test; 2) statistical test: difference between two independent means; 3) tail(s): two-tailed test; 4) type of power analysis: sensitivity; 5) alpha: 0.05; 6) power: 0.80; and 7) sample size (i.e., the total number of GPs) for control and intervention groups used in this trial. Once the effect size is found, the estimated ICC can be generated using the following formula, designed for cluster RCTs: *N =* N_sg_ (1 + (m-1) ICC), where:
*N =* number of participants in the trial (i.e., the total number of GPs);N_sg_ = number of participants in the trial, without considering clusters;m = number of participants in the cluster (i.e., the average number of GPs in the cluster);ICC = intra-cluster correlation (i.e., the correlation among GPs in the cluster).

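### The stated between-arm t-tests make no use of the T-1 scores collected in both arms; the test is valid but gives up precision

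*Protocol article*

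**What the plan says.** All citations are to the protocol article.

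- **Data collection and methods.** At baseline, "GPs in both groups will be administered the 5 questionnaires (i.e., socio-demographic, knowledge, attitudes, self-efficacy and mental health practice"). After the intervention group's training, at T-2, "both the intervention and control groups will be administered the same questionnaires, minus the socio-demographic questionnaire". Each GP who answers both times therefore supplies the same outcome scores before and after, in both arms. For the control group, T-2 also "will serve as the pre-training measure for this group, also a way to maximize our sample".
- **Statistical methods.** The between-arm analysis is "T-tests on the difference in cluster means between the intervention and control groups [53] will be assessed for the questionnaires administered to the GPs", two-sided at 0.05. An individual-level version divides the t value by the square root of the design effect. No covariate, change score or other use of T-1 is named. The same section says: "All participants will be included in the analysis".
- **Sample size.** Recruitment is raised from 15 to 19 GPs per delegation "to be sure we account for a maximum of 20% attrition rate per cluster". Effect size and ICC are described as unavailable when the protocol was written.
- **Study setting and Allocation sequence generation.** There are 38 delegations, 22 in Tunis and 16 in Sousse. They are randomised in fixed blocks of 3, and no stratification by governorate is stated.

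**The concern.** A GP's score before training usually predicts the score afterwards, and so does a delegation's mean. The trial pays to collect T-1 in both arms, yet the stated test does not use it. With only 38 units randomised and no stated stratification, the arms may differ at T-1 by chance, and neither the design nor the test as described adjusts for this.

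What is at stake is precision. The delegations are all those in the two governorates, so the trial cannot buy precision with more clusters there. Statistical methods itself worries that the cluster-level test understates power; adjusting for T-1 is a direct remedy from data already planned. The trial also sets out to estimate an effect size for the later country-wide evaluation, and a more precise estimate serves that purpose.

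**Working it through.** **1. The plan's own figures.** 15/(1 − 0.20) = 18.75, rounded up to 19; 19 × 38 = 722. Both reproduce. There is no power-based sample size to reproduce.

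**2. Which comparison is meant.** The article names no time point for the t-tests. T-2 is the only post-training assessment at which the control group is still untrained: T-3 is for the control group alone, and by T-4 both groups have been offered training. I therefore take T-2 as the randomised contrast.

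**3. Variance with and without T-1.** Assumptions, none given in the protocol: T-1/T-2 correlation r of 0.3, 0.5 or 0.7, the same at delegation and GP level; 19 delegations per arm; equal variance at both times. Relative to the unadjusted test, the variance factor is 1 − r² for ANCOVA and 2(1 − r) for a change score.

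| r | ANCOVA | Change score | Unadjusted relative to ANCOVA |
|---|---|---|---|
| 0.3 | 0.91 | 1.40 | 1/0.91 = 1.10 |
| 0.5 | 0.75 | 1.00 | 1/0.75 = 1.33 |
| 0.7 | 0.51 | 0.60 | 1/0.51 = 1.96 |

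Estimating the slope from 38 delegations adds an expected factor of 1 + 1/(38 − 4) = 35/34, about 3%, which the table leaves out.

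**4. Minimum detectable effect at 80% power.** Assume ICC 0.01, 0.05 or 0.10 and 15 GPs analysed per delegation. The variance of a delegation mean, in SD units, is ICC + (1 − ICC)/15. At ICC 0.05 this is 0.05 + 0.95/15 = 0.113, so the standard error of the arm difference is √(2 × 0.113/19) = 0.109. The noncentral t distribution (36 df unadjusted, 35 adjusted) gives:

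| ICC | Unadjusted | r = 0.3 | r = 0.5 | r = 0.7 |
|---|---|---|---|---|
| 0.01 | 0.258 | 0.246 | 0.223 | 0.184 |
| 0.05 | 0.314 | 0.300 | 0.273 | 0.225 |
| 0.10 | 0.374 | 0.357 | 0.324 | 0.267 |

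At an effect where the unadjusted test has 80% power, the adjusted test has 83.5%, 89.8% or 97.5%.

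**5. Attrition.** At exactly 20%, 0.20 × 722 ≈ 144 GPs would lack a later score. If 15 of 19 remain in each delegation, 15 × 38 = 570 remain and 722 − 570 = 152 do not. Both figures are upper scenarios, since 20% is stated as a maximum.

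**6. Does the remedy keep its error rate?** A mixed model of T-1 and T-2 with random delegation and GP effects only assumes that delegation effects are identical at both times. It was simulated with no training effect, 19 v 19 delegations, 15 GPs each, GP-level correlation 0.5 and 35 df (all assumed). At ICC 0.05, type I error was 4.7%, 6.7% and 10.3% for delegation-level correlation 1.0, 0.8 and 0.5. At ICC 0.10 it was 9.8% and 16.0% for 0.8 and 0.5. The plain t-test stayed between 3.2% and 5.3%. In a further run of the same settings (800 data sets each), adding a delegation-by-time effect brought the mixed model to between 3.0% and 6.4%; delegation-level ANCOVA gave 3.9% to 6.1%.

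**The case against.** **The unadjusted test is valid.** This stands. Randomisation makes it unbiased, and chance differences between delegations are already in the between-delegation variance and so in the standard error. The point is about efficiency.

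**Covariates are commonly left to the analysis plan.** This has some force, since the article is condensed and names no time point. But it fixes the test, the sidedness, the alpha and an individual-level variant; the comment is on that stated method. If the difference in cluster means was meant as a change from T-1, step 3 shows that this is no safe substitute. The remark about using the control group's T-2 as its pre-training measure does not fill the gap, because no analysis built on it is described.

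**The correlation may be low.** This stands too. The self-efficacy questionnaire was developed for this trial and the knowledge questionnaire was adapted, with no reliability given for either. At r = 0.3 the variance falls by only 9%.

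**A stronger reading is tempting.** A reader might infer that GPs lost to follow-up are dropped and that the plan therefore breaks its own rule: "All participants will be included in the analysis. This type of analysis is called intention-to-treat". The documents do not support that. Nowhere does the article say that these GPs are excluded, missing-data handling may sit in a document not shown, and analysing GPs as randomised with some outcomes missing does not abandon intention-to-treat. At most, a t-test on observed T-2 means cannot by itself include every participant if attrition reaches the level allowed for.

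**Conclusion.** The point holds as one of precision. The stated t-tests, at cluster level or deflated by the design effect, make no use of T-1 scores that both arms provide. If r is 0.3, 0.5 or 0.7, adjusting would leave about 91%, 75% or 51% of the variance. The gain is small at the low end and substantial from 0.5. These figures rest on an undocumented r taken as equal at delegation and GP level; the detectable effects also rest on assumed ICCs, and both on an assumed 19:19 split. The planned test is not biased or invalid, and no breach of intention-to-treat is shown. The change is recommended because it costs almost nothing; the trial does not fail without it.

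**What to change.** Replace the unadjusted t-test with one of the following, fixed before the T-2 data are seen.

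1. **Delegation-level ANCOVA (simplest).** Regress the delegation mean T-2 score on arm and delegation mean T-1 score, optionally with governorate. This costs one degree of freedom, or two with governorate, out of 36. It needs observed T-2 scores, so GPs with T-1 only do not contribute an outcome unless imputed.
2. **Mixed model of T-1 and T-2 scores.** Use a common baseline mean across arms, an arm effect at T-2, random delegation, delegation-by-time and GP effects, and small-sample degrees of freedom. The delegation-by-time effect should not be left out, for the reason in step 6. This model can keep GPs who have only a T-1 score, under a stated missing-at-random assumption. That does not restore the information lost with their T-2 scores.

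The two are not interchangeable on missing data, so the plan should name one as the main analysis. It should also say which time point the main comparison uses and how all participants are to be included when some lack T-2. The cost is wording and a slightly more complex analysis; no new data are needed.

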### Participants, interventions and outcomes

#### Study setting

To assess the potential value of capacity building by training GPs in Tunis and Sousse using an adaptation of the mhGAP-IG (version 1.0), a cluster randomized controlled trial (RCT) with two arms (i.e., intervention and control) will be conducted. Tunis and Sousse have been chosen as they regroup the majority of the Tunisian population; they have access to the only standing mental health hospital in the country, as well as psychiatric units located in general hospitals; and in this area, there are substantially more resources allocated to mental healthcare (i.e., doctors, clinics, medication) than in other areas of Tunisia. Delegations (i.e., designated areas within the governorates) have been chosen as the clusters for this trial, seeing as health services are organized accordingly in Tunisia. There are 22 delegations in Tunis and 16 in Sousse, for a total of 38 delegations.

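### As written, the optional design-effect division is applied to t-tests on delegation means, so it corrects for clustering twice and cannot give the gain in significance that the text expects

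*Protocol article*

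**What the plan says.** All quotes are from the protocol article, Statistical methods, unless noted.

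- The planned analysis is "T-tests on the difference in cluster means between the intervention and control groups", with this criterion: "Two-tailed P values of less than 0.05 will be considered statistically significant".
- The section then says that in these cluster-level tests "individual level analysis is discarded, which can underestimate the power of the analysis and generate misleading conclusions about the intervention".
- As the remedy, "Adjustments can be made to the t-tests in order to account for individual level analysis". The cited source is said to "suggest that the t-test values (i.e., the differences between groups) should be divided by the square root of the design effect", and the design effect is 1 + (m-1) ICC.
- The 0.05 criterion is repeated, and the section closes: "Individual level analysis will result in a higher significance level, compared with cluster level analysis".
- Study setting gives the number of clusters: "There are 22 delegations in Tunis and 16 in Sousse, for a total of 38 delegations".

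No t-test on individual GP scores is defined anywhere in the article.

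**The concern.** A t-test on delegation means takes its standard error from the spread of those means. That spread already contains the between-delegation variance, so the clustering is fully accounted for. Division by the square root of the design effect belongs to a different statistic: a t computed on individual GPs as if they were independent. The section names only the first kind of test and applies the divisor to it.

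Three things follow from the wording.

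1. Followed literally, the adjusted test corrects for clustering twice and is too conservative.
2. The step works against its own rationale. It is offered because the cluster-level test is thought to lose power, but for any positive ICC the divisor exceeds 1, so |t| falls and the p value rises.
3. The divided quantity is described as the difference between groups. A t value is not a difference. Dividing the difference would change the effect estimate, and estimating the effect size is a stated aim of the trial (Objectives; Sample size).

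**Working it through.** **Inputs.** 38 delegations (Study setting). Average cluster size 15, raised to 19 for 20% attrition (Sample size). Two-sided alpha 0.05 (Statistical methods). The article gives no ICC, so 0.01 to 0.20 is an assumption. The allocation ratio is not given as a number, so 19 against 19 delegations is assumed, which leaves 38 - 2 = 36 degrees of freedom.

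**The plan's own figure.** 15 / 0.80 = 18.75, rounded up to 19, and 38 × 19 = 722. This matches Table 1. There is no power figure to reproduce.

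**Literal reading: delegation-mean t divided by √DE.** DE = 1 + (m-1) ICC. The 5% critical value on 36 df is 2.028.

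- True size = 2·P(t₃₆ > 2.028·√DE).
- Power = P(t₃₆(λ) > 2.028·√DE), where λ is the noncentrality that gives the undivided test 80% power.

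Example, m = 15 and ICC 0.05: DE = 1 + 14 × 0.05 = 1.70, √DE = 1.304, and the effective critical value is 2.028 × 1.304 = 2.64. The size is 0.012 and the power 0.60.

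| m | ICC | DE | True size | Power (from 80%) |
|---|---|---|---|---|
| 15 | 0.01 | 1.14 | 3.7% | 76% |
| 15 | 0.05 | 1.70 | 1.2% | 60% |
| 15 | 0.10 | 2.40 | 0.3% | 41% |
| 15 | 0.20 | 3.80 | 0.03% | 17% |
| 19 | 0.01 | 1.18 | 3.4% | 75% |
| 19 | 0.05 | 1.90 | 0.8% | 54% |
| 19 | 0.10 | 2.80 | 0.2% | 32% |
| 19 | 0.20 | 4.60 | 0.01% | 10% |

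With m = 19, a delegation-mean result at p = 0.01 becomes p = 0.017, 0.056, 0.113 or 0.213 at the four ICC values. Without the division, the simulated type I error of the delegation-mean test at m = 19 is 4.7 to 5.1%.

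**Alternative reading: individual-level t divided by √DE.** Write σ² for the total variance of a GP score.

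- Variance of the difference in delegation means: (2/19)·σ²·[ICC + (1-ICC)/m] = (2/(19m))·σ²·DE.
- Naive individual-level variance: (2/(19m))·σ². Dividing t by √DE is the same as multiplying this variance by DE.

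With equal cluster sizes the two variances are the same, so the two t values are almost equal (simulated median ratio about 1.00). What differs is the reference distribution: 38 × 15 - 2 = 568 df instead of 36. With an ICC estimated from the same data, the t still behaves roughly like one on 36 df, so the type I error is about 2·P(t₃₆ > 1.964) = 5.7%. Simulations gave about 5 to 6%.

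**Unequal cluster sizes.** Simulated with mean size 15, an assumed coefficient of variation of 0.5, an estimated ICC and GP-based df, the adjusted individual-level test had power of about 0.8. The delegation-mean test had 0.71, 0.74 and 0.76 at ICC 0.01, 0.05 and 0.10. Part of the gain at the higher ICCs is inflation: the type I error is about 5% at ICC 0.01 but about 7 to 8% at 0.10.

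**Dividing the difference.** At m = 15 and ICC 0.05, 1 - 1/1.304 = 0.23, so the estimate would shrink by 23%.

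**The case against.** The strongest defence is that the section contrasts cluster-level with individual-level analysis throughout. On that view it meant two tests: one on delegation means, and one on individual GPs divided by √DE. The second is a standard single correction, and only this reading fits the closing sentence, since dividing the delegation-mean t can never make it more significant. The step is also permissive (it can be made), while the delegation-mean test is the one committed to. This stands in large part. It makes double correction a consequence of the text as written, not a proven intention. It does not repair the text, because the test to which the divisor would properly apply is never defined.

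Some stronger readings are tempting, but the article does not support them.

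- **The main test is invalid or severely conservative.** The delegation-mean t-test holds its level, and only the optional step is affected.
- **The p values are wrong on every reading.** The individual-level reading is close to nominal with equal clusters.
- **The individual-level test would go uncorrected**, with type I error of about 13% at a true ICC of 0.05 or 21% at 0.10 (m = 15). That needs an ICC of zero, deduced from the Sample size formula. Statistical methods does not say which ICC enters the divisor.
- **The reported difference will be shrunk.** The object named is the t value. The gloss is wrong, but nothing says that the published difference will be divided.
- **The closing sentence is simply false.** Table 1 gives 19 GPs as an average, and with unequal clusters some real power gain is possible. The phrase could also mean a larger p value, though the preceding remark about underestimated power points the other way.
- **The lack of a named primary test is an error.** That may be settled in an analysis plan that is not shown.

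**Conclusion.** The point holds as a fault in a stated rule. As written, the divisor is attached to the wrong statistic, the t value is confused with the difference, and a gain in significance is promised that the divisor cannot give to the tests it names.

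The size of the harm on the literal reading depends on an ICC that the article does not give. It is small at 0.01, substantial at 0.05 and severe at 0.10 or above. The figures assume 19 against 19 delegations of equal size. On the individual-level reading the method is roughly valid. With equal clusters, the smaller p value then comes almost entirely from GP-based instead of cluster-based degrees of freedom. The closing sentence is therefore unsupported as a general statement. The wording should be settled before analysis, because it decides which p value is reported.

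**What to change.** State one analysis with one clustering correction:

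- Keep the delegation-mean t-test (36 df with 19 against 19 delegations) with no further division; or
- Replace it with one individual-level analysis, for example a linear mixed model on GP scores with a random delegation intercept and small-sample degrees of freedom (Kenward-Roger or Satterthwaite). This is the more attractive choice if cluster sizes turn out very unequal.

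If the √DE method is kept as a check, apply it only to a t statistic computed on individual GPs and never to the difference, with an ICC estimated from the trial data and cluster-based degrees of freedom. Delete the gloss that equates the t value with the difference between groups, and delete the sentence promising higher significance.

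The cost is a few sentences in the protocol or analysis plan. No new data and no change to the design are needed.

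### The design-effect division is attached to t-tests on delegation means, which already allow for clustering, and the divided quantity is mislabelled as the group difference

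*Protocol article*

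**What the plan says.** In the protocol article, the Statistical methods section defines one between-group test for the GP questionnaires: "T-tests on the difference in cluster means between the intervention and control groups". The decision rule is "Two-tailed P values of less than 0.05 will be considered statistically significant".

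The section then remarks that these tests set individual-level information aside and may lose power, and continues: "Adjustments can be made to the t-tests in order to account for individual level analysis". The adjustment is that "the t-test values (i.e., the differences between groups) should be divided by the square root of the design effect", with the "design effect (i.e., 1 + (m-1) ICC"). The same 5% rule is then repeated, and the paragraph ends: "Individual level analysis will result in a higher significance level, compared with cluster level analysis".

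The Study setting section gives the clusters: "There are 22 delegations in Tunis and 16 in Sousse, for a total of 38 delegations". The Sample size section gives their size: "we aim to recruit 19 GPs per delegation, to be sure we account for a maximum of 20% attrition rate per cluster". It gives no ICC, because none was available when the protocol was written.

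**The concern.** A t-test on delegation means takes its standard error from the spread of those means, which includes the between-delegation variance. It needs no further correction for clustering. The divisor √(1+(m−1)ICC) belongs to a t-test on individual GP scores that ignored the delegations. The only t-tests the section defines are those on delegation means, so an analyst following the words would divide a statistic that is already correct.

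The gloss in brackets adds a second problem. It identifies the t value with the between-group difference. A t value is the difference over its standard error. The design effect inflates the standard error and leaves the difference alone.

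At stake is the test that decides significance. Two procedures can be read from the paragraph, both carry the same 5% rule, and the paragraph does not say which decides.

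**Working it through.** **Inputs from the protocol.** 38 delegations; average 15 GPs per delegation before the attrition allowance, 19 recruited; two-sided alpha 0.05. The plan's own figures reproduce: 15/0.80 = 18.75, rounded up to 19; 38 × 19 = 722.

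**Assumptions.** 19 v 19 delegations, equal sizes, m = 15 analysed, total SD 1, ICC 0.01 / 0.05 / 0.10. The protocol gives neither the split nor an ICC.

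**Step 1: the delegation-mean test already contains the design effect.** Let DE = 1+(m−1)ICC. A delegation mean has variance ICC + (1−ICC)/m = DE/m, so with k = 19 per arm the standard error of the difference is √(2·DE/(m·k)). At ICC 0.05, DE = 1 + 14 × 0.05 = 1.70 and SE = √(2 × 1.70/285) = 0.109. An individual-level test that ignores clustering uses √(2/285) = 0.084. Multiplying that by √1.70 = 1.304 gives the same 0.109. Dividing the delegation-mean t by 1.304 amounts to using 0.109 × 1.304 = 0.142.

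**Step 2: effect on the test.** Dividing t by √DE and comparing with 2.028 (36 df) is the same as requiring |t| > 2.028 × √DE. Type I error comes from the central t. Power comes from the noncentral t (upper tail), for an effect that has 80% power on the undivided test.

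| ICC | DE | √DE | Effective cutoff | Type I error | Power (80% undivided) |
|---|---|---|---|---|---|
| 0.01 | 1.14 | 1.068 | 2.165 | 3.7% | 76% |
| 0.05 | 1.70 | 1.304 | 2.644 | 1.2% | 60% |
| 0.10 | 2.40 | 1.549 | 3.142 | 0.3% | 41% |

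With m = 19 the figures are 3.4% / 0.8% / 0.2% and 75% / 54% / 32%.

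**Step 3: the alternative reading.** Simulation of 20,000 null trials (m = 15, ICC 0.05, true ICC used in the divisor) gave these type I errors:

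- delegation-mean t, undivided: 5.0%
- delegation-mean t divided by √DE: 1.3%
- individual-level t, undivided: 13.1%
- individual-level t divided by √DE: 5.1%

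So one division is right for an individual-level t and wrong for a delegation-mean t. Power at a difference of 0.314 SD (3,000 simulated trials) was 79.6% for delegation means, 81.2% for the divided individual-level t on 568 df (38 × 15 − 2), and 59.2% for the divided delegation-mean t.

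**Step 4: where the small gain comes from.** With equal sizes the divided individual-level t is essentially the delegation-mean t (step 1). The two differ mainly in the reference distribution: 1.964 at 568 df against 2.028 at 36 df. If the ICC has to be estimated from the same 38 delegations, the 568-df cutoff is too lenient: P(|t₃₆| > 1.964) = 5.7%.

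**The case against.** The strongest reply is that the double correction is not clearly planned. The test that will be done is the delegation-mean t-test, which is valid. The adjustment is worded as something that can be made, its stated purpose is individual-level analysis, and the last sentence contrasts individual-level with cluster-level analysis. Dividing a delegation-mean t could only raise the P value, which defeats the paragraph's aim of recovering power. An adjusted t-test on individual scores is therefore a plausible intent, and for that test the division is correct. This stands. What remains is that no such test is written down.

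The remark that cluster-level tests can lose power is also defensible. The protocol gives 19 only as an average. Take 19 v 19 delegations, mean size 15, an assumed size CV of about 0.7, a size-weighted m in the design effect and 36 df for both tests. Simulated power for the delegation-mean t against the divided individual-level t was then about 58% v 76% at ICC 0.01, 64% v 72% at 0.05 and 68% v 69% at 0.10, with type I error of about 4% for the latter. A reader might infer that the closing sentence is false on every reading. It is not: on the individual-level reading there is a small gain with equal sizes, and a larger one when sizes vary and the ICC is low.

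A reader might also infer that the rule biases the effect size the trial promises for country-wide planning. The protocol does not support that. The Sample size section takes that figure from a G*Power sensitivity calculation based on alpha, power and group sizes, and no divided difference enters it. Dividing a reported mean difference would shrink it by 6% / 23% / 35% at the three ICCs (1 − 1/√DE, m = 15), but the Statistical methods section describes no adjusted estimate; that reading rests on the bracketed gloss alone.

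Finally, the literal error is conservative and modest if the ICC is near 0.01.

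**Conclusion.** The paragraph is wrong as written and needs correcting. It should not be described as an unambiguous plan to correct twice. Taken literally it gives a test at about 3.7% / 1.2% / 0.3% instead of 5% and cuts 80% power to about 76% / 60% / 41% at ICC 0.01 / 0.05 / 0.10. At ICC 0.05 the two available readings differ by about 22 points of power (81.2% − 59.2%). On the charitable reading nothing is corrected twice, but the gloss is still an error, and with equal delegation sizes the gain over the delegation-mean test is small and mainly a matter of df. The sizes rest on the assumed 19 v 19 split, equal delegations of 15 and the assumed ICCs. The direction does not: for any ICC above zero, dividing a delegation-mean t makes the test conservative. The effect size promised in the Sample size section is not affected by this point.

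**What to change.** Reword the second paragraph of Statistical methods:

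- State that the t-test on delegation means is used undivided, with 36 df if all 38 delegations contribute.
- If the design effect is kept, state that it applies only to the t statistic (equivalently, the standard error) of a t-test on individual GP scores, referred to clusters-minus-2 df.
- Delete the bracketed gloss on the t-test values and report mean differences undivided.
- Remove the closing sentence on significance, or qualify it: any gain is small with equal delegation sizes and depends on how much sizes vary and on the ICC.
- Name which of the two analyses is primary, before outcome data are seen.

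The cost is wording only. The sample size of 722, the data collection and the software are unchanged.
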